### Walking trials

Biomechanical gait analysis will be measured using eight Miqus M5 Qualisys cameras (Qualisys, Sweden), two video cameras, and one portable Kistler force plate (Kistler, Switzerland) to examine movement patterns and loads acting on the joints during level walking over a distance of 10-metres. Each participant will complete twelve walking trials per session (6 trials hitting the force plate with prosthetic limb and 6 trials with the sound limb). Non-invasive reflective markers (n = 54; Fig 2) will be placed on the participants before starting data collection in the anatomical locations listed in S1 Table, and in line with the methods by Silverman and colleagues [56]. Reliability for marker placement in a similar demographic population in terms of BMI (age-matched BMI above the 97th percentile) has been assessed by Horsak and colleagues [57]. The standard error of measurement (SEM) was below 5° for all participants (n = 11) for 28 kinematic parameters measured, including anterior pelvic tilt, pelvis rotation, and hip and knee flexion. Furthermore, 23 parameters displayed acceptable ICCs (≥0.70), and the remainder showed moderate values.

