### Study outcomes

Participants will start the protocol as soon as they are fitted with the prosthesis and they are able to walk (approximately 0-3-months post-amputation). The independent variable of this study is the time course (12-months) with measurements taken every 3-months for 12-months (5 visits in total). The biomechanical and psycho-social variables reported in Table 2 represent the dependent variables. Preliminary pilot tests have been performed in the clinical setting on able-bodied participants.

**Table 2 pone.0314523.t002:** Full list of biomechanical and psycho-social variables for analysis.

Variables	Outcome measures
Bio-behavioural	Lower-limb and lumbar kinetics (e.g. joint reaction forces)
	Lower-limb kinematics, including lumbopelvic and lower-limb region movement asymmetries (e.g. joint angles)
	Trunk and lower-limb muscle activations and timings
	Body centre of mass position and symmetry indices
	Temporal-spatial characteristics of gait (e.g. stride length, walking speed)
	Lower-limb-length discrepancies
	Pain intensity/location/type
Psycho-social	Pain attention and interference
	Fear of movement
Psycho-social	Physical activity and quality of life scores
	Anxiety and depression
Other	Anthropometric measurements, socket comfort, prosthesis type, presence of blisters

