### Study procedures

Basic anthropometric data (mass, height) will be recorded for each participant before starting the motion capture sessions. Participants will wear their own passive prosthesis, and will perform a static, standing calibration trial in the anatomical position followed by twelve 10-metre gait trials at a comfortable self-selected velocity and six sit-to-stand movements from a chair. A good walking trial will require participants to walk at constant velocity with the foot within the boundary of the force plate. During the sit-to-stand tests, participants must have their feet placed shoulder width apart on the force plate and rise from the chair without the use of the hands/arms.

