### Data analysis

Marker trajectories and GRF data during the walking and sit-to-stand trials will be processed using a 4^th^-order Butterworth filter with a cut-off frequency of 6 Hz. One complete gait cycle per walking trial will be analysed. Joint kinematic and kinetic data will be time-normalised to 101 sample points per gait cycle. The start of the gait cycle is defined as the instant when the foot hits the platform and the end of the gait cycle is defined by the method proposed by De Asha and colleagues [67]. Joint range of motion will be calculated as the difference between the maximum and minimum angles during a gait cycle. Initial heel-strike and toe-off will be detected from the force trace as a single force platform will be used for all trials. Initial heel-strike will be detected as the first instance of force production, and toe-off will be defined as the final data point of force production. End heel-strike of a single gait cycle will be defined by the time-point of peak hip extension of the contralateral limb [67]. Raw EMG signals will be band-pass filtered between 30 and 400 Hz, full-wave rectified, and low-pass filtered (6 Hz) to create a linear envelope [59, 68]. The peak EMG signals of the trunk and sound lower-limb muscles during sit-to-stand trials will be used to normalise EMG data from the walking and sit-to-stand trials for each individual.

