A 3D full-body TTA and TFA musculoskeletal model (38 degrees of freedom), modified from the validated model described by Rajagopal and colleagues [69], will be used for muscle-driven simulations of gait (Fig 3). The musculoskeletal models were developed in OpenSim 4.3 and includes a total of 324 musculotendon actuators. To model the trunk and pelvis, markers will be placed over the T12 and C7 spinous processes, the first sacral vertebrae, and bilaterally over the anterior superior iliac spine and posterior superior iliac spine. Additionally, a marker cluster will be placed on the lumbar spine region between the T12 and S1 markers. The models will be scaled in size and body mass to each participant using a static, standing calibration trial. The prosthetic limb will be scaled by positioning a marker at the bottom of the socket where it meets the pylon, allowing the pylon and the residual limb to be scaled with different scaling factors [70]. Data will be processed in OpenSim for the calculation of joint kinematics (inverse kinematics) and kinetics (inverse dynamics and joint reaction analysis), using information from the muscles activation (EMG-informed analyses; [71]). A full list of the variables measured for analysis was presented previously in Table 2.

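### With one force plate, lumbar joint reaction force in walking has complete external forces only during plate-limb single support, yet kinetics are planned over the whole gait cycle

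*Protocol article*

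**What the plan says.** The protocol article fixes five things that bear on this.

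- **Equipment.** Walking trials: "one portable Kistler force plate (Kistler, Switzerland) to examine movement patterns and loads acting on the joints during level walking". The Data analysis section repeats it: "Initial heel-strike and toe-off will be detected from the force trace as a single force platform will be used for all trials".
- **Trials.** Twelve per session: "6 trials hitting the force plate with prosthetic limb and 6 trials with the sound limb". Under Study procedures, a good trial requires the participant to "walk at constant velocity with the foot within the boundary of the force plate".
- **Analysis window.** Data analysis: "One complete gait cycle per walking trial will be analysed", and "Joint kinematic and kinetic data will be time-normalised to 101 sample points per gait cycle". The cycle begins at contact with the plate, so it belongs to the limb that strikes it.
- **Method.** Data analysis: a full-body model with 38 degrees of freedom and 324 musculotendon actuators "will be used for muscle-driven simulations of gait", with inverse dynamics and an EMG-informed joint reaction analysis.
- **Outcome.** Table 2 under Study outcomes: "Lower-limb and lumbar kinetics (e.g. joint reaction forces".

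The article gives no narrower window for lumbar kinetics and no means of supplying the force under the foot that is off the plate.

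**The concern.** Each choice is reasonable alone. Together they ask a whole-body model to produce lumbar joint reaction forces over a full cycle when, for much of that cycle, one loaded foot has no recorded force.

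A joint reaction force of this kind is the net load plus the contribution of the muscles acting across the joint. Some of those muscles cross both the hip and the lumbar spine, so their estimated forces must also satisfy the hip moments. On the non-plate side the hip moment is incorrect whenever that foot is on the ground.

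Lumbar loading is one of the candidate explanatory variables for lower back pain. How many frames are affected depends on stance and double-support time. HA1 expects gait to change with time since amputation, and HA4 links slower gait to pain and function. Any error could therefore vary with timepoint and with pain, which are the terms of interest in the mixed models, and could also enter the random forest step.

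**Working it through.** The protocol states no figure for this point, so there is none to reproduce. The check has two parts: how much of the cycle lacks a force, and where the missing force goes.

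**1. Share of the cycle with an unmeasured loaded foot**

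Assumption: stance occupies 58-70% of the cycle for each limb. From the protocol: one plate, a cycle starting at plate contact, 101 points.

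Let s_p be the stance share of the plate limb and s_o that of the other limb.

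- Other foot loaded but unmeasured = s_o
- Total double support = s_p + s_o − 1
- Plate-limb swing = 1 − s_p
- Plate-limb single support, the only window in which every ground force is known = 1 − s_o

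| s_p | s_o | Double support | Plate-limb single support | Other foot loaded | Points of 101 affected |
|---|---|---|---|---|---|
| 0.58 | 0.58 | 0.16 | 0.42 | 0.58 | 59 |
| 0.60 | 0.60 | 0.20 | 0.40 | 0.60 | 61 |
| 0.60 | 0.65 | 0.25 | 0.35 | 0.65 | 66 |
| 0.65 | 0.60 | 0.25 | 0.40 | 0.60 | 61 |
| 0.65 | 0.65 | 0.30 | 0.35 | 0.65 | 66 |
| 0.70 | 0.70 | 0.40 | 0.30 | 0.70 | 71 |

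Check on the first row: double support 0.16 + plate-limb swing 0.42 = 0.58, the other limb's stance share.

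External forces are complete for 30-42% of the cycle and incomplete for 58-70%. The third and fourth rows show that, when the two limbs differ in stance time, the complete window differs between prosthetic-limb and sound-limb hits.

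**2. Where the missing force goes**

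A quasi-static vertical balance, in units of body weight (BW). Assumed weights: 0.55 above the lumbar joint, 0.12 pelvis, 0.165 each leg (0.55 + 0.12 + 2 × 0.165 = 1.00). F is the share of body weight on the plate foot; the other foot's 1 − F is not recorded.

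- Solved from the feet up: net lumbar force = F − 2 × 0.165 − 0.12 = F − 0.45
- Solved from the trunk down: net lumbar force = 0.55, and pelvis residual = 1 − F

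| F | Feet up, one force missing | Trunk down | Pelvis residual (trunk down) |
|---|---|---|---|
| 1.0 (plate-limb single support) | 0.55 | 0.55 | 0.0 |
| 0.5 (double support, equal share) | 0.05 | 0.55 | 0.5 |
| 0.0 (plate-limb swing) | −0.45 | 0.55 | 1.0 |

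The net lumbar load therefore survives in a trunk-down solution and fails in a feet-up one. The article does not say which is used.

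**3. From net load to joint reaction force**

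The trunk-down result covers net load only. The listed outcome is a joint reaction force from a muscle-driven model. The part contributed by muscles crossing hip and lumbar spine is constrained by both hip moments, and the non-plate one is incorrect in the frames counted in step 1. The size of this error depends on the model's muscle paths and on how the EMG-informed solution shares force. The article does not allow it to be calculated.

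**4. What is unaffected**

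For the limb on the plate, force is measured in stance and is zero in swing. Its ankle, knee and hip kinetics are supported at all 101 points.

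**The case against.** The case on the other side is substantial, and much of it stands.

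- **Limb kinetics.** A reader might infer that half of the lower-limb kinetics are invalid. The article does not support that. It nowhere plans to take kinetics of the non-plate limb from a trial. Each limb has six plate trials of its own, so sound-versus-prosthetic loading remains obtainable, though from different trials.
- **Lumbar load.** A reader might infer that all lumbar kinetics are wrong. They need not be: no ground force acts on the trunk, and net lumbar force and moment can be solved from trunk and arm motion. This stands for net load. It does not cover the muscle contribution to the joint reaction force that Table 2 names.
- **Size.** Counting frames with an unmeasured foot is not the same as measuring an error in lumbar force. This stands. The 58-70% is the share of the cycle without complete forces, and the missing force of up to one body weight is a ground force.
- **Importance.** Lumbar reaction force is named in no hypothesis, forms part of one Table 2 row, and is not the basis of the sample size, which rests on kinematics. This also stands and limits the weight of the point.
- **Condensed article.** Foot-force reconstruction and residual checks may sit in the full protocol, and the six-plus-six design already supplies the data for them. However, the Data analysis section goes into filter cut-offs and adapts event detection to the single plate, while setting full-cycle kinetics without a matching limit. Followed as written, that rule yields unsupported lumbar values.
- **EMG.** The EMG-informed step may offer some protection. It is partial: the Fig 2 caption places the thigh sensors on the sound limb, so on that reading they give no information about the prosthetic side when the sound limb is on the plate.

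**Conclusion.** The point holds in a limited form. Outside plate-limb single support, lumbar joint reaction force from the walking trials is not supported by complete external forces. That is about 58-70% of the analysed cycle (59-71 of 101 points) if stance is 58-70%, which is an assumption. Whether the net lumbar load is also affected depends on the direction of solution, which the article leaves open. The muscle contribution is affected in either case, by an amount that cannot be derived here.

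It would go too far to say that the design produces false time trends or false associations with lower back pain. The route exists, because stance timing may change with recovery and pain, but nothing in the article lets one calculate such a bias. This is an inexpensive improvement to make before lumbar loading is analysed. It does not undermine the limb-level kinetics or the study as a whole.

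**What to change.** Keep full-cycle kinetics for the limb on the plate. For lumbar joint reaction force, choose and state one of these:

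1. **Restrict the window.** Report it over plate-limb single support only, once from the prosthetic-limb hits and once from the sound-limb hits.
2. **Reconstruct the missing force.** Take the other foot's force from the same participant's opposite-limb trials at the same visit, time-aligned at heel-strike and matched on walking speed. Set in advance a limit on the pelvis residual, as a share of peak ground reaction force, and exclude frames that exceed it.
3. **Narrow the outcome.** If only net lumbar load solved from the trunk down is intended, say so and amend the joint reaction wording in Table 2.

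All three need only processing and wording changes, with no extra equipment, trials or patient time. The cost of the first is a shorter window for lumbar loading. The second relies on a reconstructed force that must pass the residual check. The third gives up the muscle-dependent joint reaction force as an outcome.

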**Fig 2 pone.0314523.g002:**
[figure not shown]
Full body marker set (left) and EMG sensors locations (right). See S1 Table for a completed list of the names of the markers. The rectus femoris and biceps femoris EMG sensors are located on the sound limb, which in this specific example is the left side. However, they are located accordingly with the side of the amputation.

Eight Delsys Trigno EMG electrodes (Delsys, MA, USA) will be positioned bilaterally on four different pairs of muscles (as displayed in Fig 2), to measure their activity. The skin will be adequately prepared by shaving and cleaning with alcohol wipes and the correct location of marker placement will be determined from the SENIAM guidelines [58]. Due to participant characteristics (poor balance and limited mobility) and time constraints (only one hour is allowed for data collection with the patients), the peak activation of each muscle during the sit-to-stand trials will be used for the EMG normalisation analysis, as other authors did in similar investigations on participants with LLA [59, 60]. Variability of EMG placement of lower-limb muscles has been assessed amongst persons with LLA by Wentink and colleagues [61]. The overall inter-subject variability was larger in persons with LLA compared to controls, with a 3% SEM of the EMG data for the stance and swing phases for controls, and 4% for persons with LLA (outliers ranging from 12–14%).

### Sit-to-stand trials

The portable Kistler force plate and the EMG system will be used to determine GRF and muscle mechanics non-invasively to identify potential risks for LBP. Six repetitions will be performed after the walking trials, with the participants still wearing the markers and EMG sensors as described before. During the sit-to-stand tests, participants must have their feet placed shoulder width apart on the force plate, must rise from the chair without the use of the hands/arms, and then hold the standing position which will mark the end of one repetition. Then following variables will be calculated; GRF, centre of pressure (coordinates), trunk kinematics (trunk angles and angular velocity), EMG muscles activity, and timing of the sit-to-stand movement (using the position of the T12 marker and hip/knee peak extension).

### Questionnaires

Participants will complete eight questionnaires, assessing pain and psychological variables (see S2 Table), using the online software Qualtrics. Patients will complete the questionnaires online within 24-hours of each testing session and the principal investigator will provide support via a phone call. Different types of LBP, including both acute and chronic LBP, will be captured from the questionnaires in order to analyse the full spectrum. Additionally, a box for free comments will be included in the questionnaires (see S2 Fig).

These measures have been validated for use amongst the chronic non-malignant pain population and are widely used in clinical settings for the treatment of chronic pain [62]. The Brief Pain Inventory (α > .70), Pain Catastrophising Scale (α = .87), and the TSK (α = .95) are valid and reliable for use with LBP patients [63–65], however reliability has not been assessed amongst persons with LLA.

### Sample size

The sample size of 30 participants was calculated using G*Power software (3.1.9.7). An *a priori* power analysis was performed based on data from a previous study examining lumbar spine kinematics and LBP amongst persons with unilateral LLA [17]. The estimated sample size was calculated to be N = 26 participants (α = 0.05, 1-b = 0.80), with an effect size of 1.03. However, due to possible challenges with recruiting and retaining participants from clinical practice environments, such as people with limb loss, it is important to account for a 10% drop-out rate [66]. Therefore, the recruitment of at least 30 participants in total will be attempted from the NHS Enablement Centres.

It is important to note that the sample size calculation takes into account only the kinematic variables, and not the relationship with the psycho-social variables measured through the online questionnaires. Ideally, a much larger population would be required for powered analysis of the psycho-social variables, however, due to the time constraints and the lack of data, the estimated sample size of N = 30 patients is the most feasible for the project duration.

### Data analysis

Marker trajectories and GRF data during the walking and sit-to-stand trials will be processed using a 4^th^-order Butterworth filter with a cut-off frequency of 6 Hz. One complete gait cycle per walking trial will be analysed. Joint kinematic and kinetic data will be time-normalised to 101 sample points per gait cycle. The start of the gait cycle is defined as the instant when the foot hits the platform and the end of the gait cycle is defined by the method proposed by De Asha and colleagues [67]. Joint range of motion will be calculated as the difference between the maximum and minimum angles during a gait cycle. Initial heel-strike and toe-off will be detected from the force trace as a single force platform will be used for all trials. Initial heel-strike will be detected as the first instance of force production, and toe-off will be defined as the final data point of force production. End heel-strike of a single gait cycle will be defined by the time-point of peak hip extension of the contralateral limb [67]. Raw EMG signals will be band-pass filtered between 30 and 400 Hz, full-wave rectified, and low-pass filtered (6 Hz) to create a linear envelope [59, 68]. The peak EMG signals of the trunk and sound lower-limb muscles during sit-to-stand trials will be used to normalise EMG data from the walking and sit-to-stand trials for each individual.

A 3D full-body TTA and TFA musculoskeletal model (38 degrees of freedom), modified from the validated model described by Rajagopal and colleagues [69], will be used for muscle-driven simulations of gait (Fig 3). The musculoskeletal models were developed in OpenSim 4.3 and includes a total of 324 musculotendon actuators. To model the trunk and pelvis, markers will be placed over the T12 and C7 spinous processes, the first sacral vertebrae, and bilaterally over the anterior superior iliac spine and posterior superior iliac spine. Additionally, a marker cluster will be placed on the lumbar spine region between the T12 and S1 markers. The models will be scaled in size and body mass to each participant using a static, standing calibration trial. The prosthetic limb will be scaled by positioning a marker at the bottom of the socket where it meets the pylon, allowing the pylon and the residual limb to be scaled with different scaling factors [70]. Data will be processed in OpenSim for the calculation of joint kinematics (inverse kinematics) and kinetics (inverse dynamics and joint reaction analysis), using information from the muscles activation (EMG-informed analyses; [71]). A full list of the variables measured for analysis was presented previously in Table 2.

**Fig 3 pone.0314523.g003:**
[figure not shown]
Example of the OpenSim musculoskeletal model for a TTA. The pink balls represent marker locations, and the red strings represent the muscles included in the model.

### Statistical analysis

All biomechanical data will be processed in MATLAB® R2023a (MathWorks, Inc) and OpenSim and reported as mean ± standard deviation. Statistical analysis will be conducted using IBM SPSS software (Version 26.0. Armonk, NY). Descriptive data obtained from anthropometrics, online questionnaires, and gait parameters will be analysed by descriptive statistical methods. Biomechanical and psycho-social data will be inputted into a random forest algorithm, which will be used as a dimensionality reduction approach to better explain the variance of the LBP data distribution [72]. Thus, this approach will allow us to evaluate how important each factor is influencing the final outcome (i.e. LBP presence). The process of feature selection is a type of exploratory analysis based on the Pearson’s *r* correlation coefficient to estimate correlations between all the variables collected and LBP. The application of random forest analysis in clinical research is considered a key step towards improving patient related health outcomes [73]. Clinical studies in the literature support the use of random forest analysis for classification performance and prediction, for example in the diagnosis of breast cancer using mammography imaging techniques [74]. Generalised linear mixed models will be used to examine the contributions from biomechanical and psycho-social variables to predict the development of LBP. The variables included in the analysis will be selected based on previous studies [17, 26, 47] and the results from the random forest analysis. Generalised linear mixed models will then be created to identify the best predictors to answer research questions two, three, and four, with pain as a ‘yes/no’ binary variable, and a linear mixed effects model will investigate research question one. Significance will be accepted at *p* < 0.05.

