### Prevalence of lower back pain amongst persons with lower-limb amputation

LBP is a serious global health problem and is considered the leading cause of disability worldwide, with 11–38% of the general population experiencing LBP over a one-year duration [13–15]. The annual cost of LBP in the United States is approximately $100 billion, with two-thirds attributed to socio-economic factors including reduced productivity [16]. LBP is an important cause of secondary disability amongst persons with LLA [17], with national annual prevalence rates in four countries (United Kingdom, United States, Sweden, and Vietnam) between 50–90% [18–23]. Following amputation, a one-month prevalence rate of 20–30% [24, 25] and a two-year prevalence of 60% [22] have been reported. Approximately 25–50% of individuals with LBP report the condition as ‘bothersome’ and experience difficulties performing activities of daily living (ADL), including ambulating and standing up from a chair [18].

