### Objectives and hypotheses

To address this gap, the proposed study protocol will explore the bio-behavioural, psychological, and social characteristics of LBP amongst persons with unilateral LLA over a period of 12-months after their amputation. The whole spectrum of LBP will be explored, including both acute and chronic LBP. To date, this has not been explored in the current literature, and is therefore a novelty and strength of the proposed protocol. Specifically, interactions between bio-behavioural factors of movement (i.e. gait characteristics, trunk and lower-limb muscle activations), and the psycho-social aspects of pain and function will be investigated. Here, the term ‘function’ refers to the comprehensive overview of each participant’s everyday interactions and long-term targets, defined by the participant in terms of person-specific activities and goals. Consideration of these variables aim to improve an understanding grounded in patient-specific function, helping to decipher the relationships between the biopsychosocial characteristics of LBP in individuals with LLA. In doing so, this investigation looks to inform tailored care management and rehabilitation processes.

We hypothesise that individuals who display fear avoidance behaviours will have altered joint range of motion, which in turn will influence muscle activation patterns, leading to greater loading on one side and asymmetries between the sound and residual limb, and therefore increase the risk of LBP development.

Hypothesis 1 (HA1): Gait characteristics will change with time post-amputation and will stabilise following a reduction in movement pattern and trunk muscle activation asymmetries.Hypothesis 2 (HA2): Individuals with a greater risk factor pattern of stressors will experience more pain following the amputation.Hypothesis 3 (HA3): Persons with LLA who experience different types of pain will be at a greater risk of reduced functionality over time.Hypothesis 4 (HA4): Greater scores on psycho-social assessment of pain questionnaires, asymmetric gait patterns, greater and asynchronous activation of trunk muscles, and changes in spatiotemporal characteristics of gait, such as slower gait speed, will be associated with altered pain and function.

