#### Research question four

Pain and function will be modelled as the dependent variable, ‘timepoint’, biomechanical, and psycho-social variables will be the fixed effects of interest, and participants will be defined as a random effect.

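### The random-forest and research-question-four models take the presence of low back pain as outcome, with no stated time ordering, so they show association and cannot support the promised prediction of its development

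*Protocol article*

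**What the plan says.** The target is development. Objectives and hypotheses sets out a directional chain from fear avoidance through joint motion, muscle activation and asymmetry, ending "and therefore increase the risk of LBP development". Study design describes the aim as pathways by which LBP develops. Statistical analysis repeats the target: "Generalised linear mixed models will be used to examine the contributions from biomechanical and psycho-social variables to predict the development of LBP".

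The modelled outcome is presence. The random forest is to show "how important each factor is influencing the final outcome (i.e. LBP presence". The mixed models use pain coded yes or no: "Generalised linear mixed models will then be created to identify the best predictors to answer research questions two, three, and four". Under Research question four, timepoint, "biomechanical, and psycho-social variables will be the fixed effects of interest, and participants will be defined as a random effect".

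Three other places matter:
- Questionnaires has participants complete the pain and psychological scales within a day of each testing session, so they describe the same visit as the gait data.
- Table 1 (Recruitment) admits people 0–3 months after amputation and has no criterion on existing LBP.
- The Introduction says that joint pain can affect gait. The section on LBP characteristics and gait treats pain as something that may alter walking performance.

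**The concern.** A model of presence on predictors from the same visit cannot say which came first. Guarded gait or a high fear score may precede LBP or follow it, and either gives the same coefficient. Nor does such a model separate a person who had LBP at visit 1 and kept it from one in whom it began during follow-up.

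The article gives reasons to keep these apart. Its section on psycho-social risk factors says such factors do not seem to predict first onset but are linked to chronic LBP, so onset and persistence may have different determinants. It also criticises earlier work for seldom accounting for pre-existing pain.

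At stake is the main message. Followed as written, the plan could present consequences of LBP as predictors of its development, and the Abstract says the results will inform care and rehabilitation.

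**Working it through.** **1. Target against model.** The stated target is development. The stated outcome is presence. Research question four lists timepoint, the two groups of variables and a participant random effect. It names no lag, no term for LBP at the previous visit or visit 1, and no onset outcome. The random effect absorbs stable differences between people and timepoint absorbs a common trend. Neither sets the direction of effect.

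**2. Which models are affected.** Research question one models gait and muscle activation over time, and research question two has timepoint as its only fixed effect. The problem therefore falls on research question four and on the random-forest ranking that feeds variable selection.

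**3. The plan's own figure.** The Sample size section gives N = 26 (α = 0.05, power 0.80, effect size 1.03). A one-sided two-sample t-test reproduces it: 13 per group, noncentrality 1.03 × √(13/2) = 2.63, 24 degrees of freedom, power 0.818. A two-sided test would have power 0.712 at that size and need 16 per group. The article states neither the test nor the sidedness. On this reconstruction it is a two-group comparison of kinematics, and it does not size any analysis of onset. Allowing for 10% drop-out, 26/0.9 = 28.9, so 29, consistent with a target of 30. With 30 recruited, 30 × 0.9 = 27 complete.

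**4. People at risk of onset.** The article does not say how many will have LBP at visit 1. Its background section reports: "Following amputation, a one-month prevalence rate of" 20–30%. Taking that as the visit-1 proportion is an assumption:
- already with LBP: 30 × 0.20 = 6 to 30 × 0.30 = 9;
- at risk of onset: 30 − 9 = 21 to 30 − 6 = 24;
- among 27 completers: 27 × 0.70 = 18.9 to 27 × 0.80 = 21.6, so about 19–22.

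The number of new cases needs a second assumption. If the share who have ever had LBP by 12 months lay anywhere in the article's annual prevalence range of 50–90% (15–27 of 30), new cases would number 15 − 9 = 6 to 27 − 6 = 21.

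**5. Can a pure consequence look like a predictor?** A simulation (1,000 runs) assumed:
- 27 people and five visits;
- 25% with LBP at visit 1, 11% onset per visit and 85% persistence;
- a gait variable that LBP shifts by 0.8 units (between- and within-person SD 0.7 each, so total SD √(0.49 + 0.49) = 0.99);
- no effect of gait on onset.

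| Analysis | p < 0.05 for gait |
|---|---|
| Same-visit presence on gait and timepoint (logistic GEE standing in for the mixed model) | 971/1000 = 97.1% |
| First onset on previous-visit gait and timepoint (logistic model, no random effect) | 32/996 = 3.2% |

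The mean number of new cases was 7.5 per run. The 0.8 shift is assumed, so the 97.1% shows what can happen and does not estimate this study's error rate.

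**The case against.** The strongest reply is that the study is exploratory and that much of its wording is already about association. Hypothesis 4, which research question four tests, speaks of variables being associated with altered pain and function, and the Abstract speaks of investigating relationships. Lag structure is also commonly left to an analysis plan, and none was available. This stands in part. The article does not state that predictors come from the same visit. That is the natural reading, given how the data are collected and the models described. What the reply does not remove is the article's own use of development for a model of presence.

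A reader might go further in several ways that the article does not support:
- *That the repeated measurements go unused.* All four research questions use timepoint and a participant effect. What is missing is use of temporal order.
- *That a third to a half of LBP cases developed nothing during the study.* This takes the 20–30% as a visit-1 rate, although one-month prevalence may be a recall period, and applies a two-year figure of 60% to 12 months. LBP that began between amputation and visit 1 is still development after amputation, and LBP present at visit 1 can still become chronic.
- *That the general-population rate adds further people with LBP before amputation.* They would overlap with those who have LBP at entry.
- *That a lagged onset model should replace the planned one.* With perhaps 6–21 onsets it would be fragile. It would also drop persistence, the outcome that the article links to fear and depression, and a three-month lag may miss short episodes.

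**Conclusion.** The point holds for the random forest and research question four. Their outcome is presence, no time ordering is stated, and people with LBP at visit 1 are not separated from new cases. Their results are associations, and the statement about predicting development is not supported by the models described.

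The mismatch of wording is certain because both sides of it are in the article. Same-visit timing is an inference. The size cannot be fixed from the documents: 6–9 of 30 already with LBP and 21–24 at risk is conditional on the 20–30% assumption, and the simulation shows only that the error is possible.

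**What to change.** 1. Describe the random-forest and research-question-four results as associations with LBP presence. Remove the claim that they predict development.
2. Report LBP status at visit 1. Report onset (LBP at a visit after none at the previous visit) separately from persistence.
3. Add a lagged analysis. Among visits where the person had no LBP at the previous visit, model LBP on one or two predictors measured at that previous visit, with timepoint, and with a participant random effect where it can be estimated. Name the predictors in advance, not from the random forest, whose ranking is against presence. Base any statement about development on this analysis only.

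The cost is wording and a re-ordering of data that the five visits already supply. The drawback is few onsets and wide intervals. With so few events the random effect may not be estimable, and a null result would not exclude an effect. The report should state both the number of onsets and this limit.
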